#### Fitbit charge 5 wearable metrics

Consumer-grade Fitbit devices, including the Charge series, have demonstrated acceptable validity and reliability for measuring steps and energy expenditure in older adults. In controlled laboratory settings, Fitbit-measured steps agreed within ± 3% of observed counts; in free-living conditions, deviations remained within approximately ± 10% of research-grade accelerometers (e.g., actigraphy [51]). Prior evidence indicates that step counts correlate well with self-reported metrics—specifically, Fitbit steps with the PASE questionnaire and Fitbit calories burned with the CHAMPS–MET metric, particularly in older adult populations [37]. While Fitbit may underestimate steps at slower gait speeds [52], overall metrics are sufficiently reliable for longitudinal monitoring in aging cohorts. Data collection from this device will consist of two steps: (1) a period of data collection while participants initially wear the Fitbit for seven consecutive days before the intervention is implemented and (2) subsequent data collection while participants continue wearing the Fitbit throughout the intervening period. Similarly to the interventions that include exercise, participants in the sleep-only group will also be asked to continuously wear the device throughout the 8-week trial duration to ensure that physical activity levels do not confound the effects of sleep.

It should be noted that there is a considerable paucity of evidence in the prevailing body of literature assessing how well Fitbit-derived metrics correlate with PASE and CHAMPS-MET scores in upper middle-aged adults (i.e., 55–64 years). As a result of this age-specific validation gap, the current trial will combine Fitbit metrics (e.g., step counts and caloric expenditure) with self-reported physical activity data from the PASE and CHAMPS questionnaires; this approach will enable a more comprehensive assessment of physical activity patterns and provide an opportunity to compare and interpret agreement between objective and self-reported measures within this cohort. The paucity of evidence that has assessed these correlations with the inclusion of middle-aged and older adult samples has generally found moderate relationships between Fitbit-derived step counts and PASE scores as well as between Fitbit-derived estimated energy expenditure and CHAMPS-derived MET values [37].

#### Elemind Neuromodulation headband

The Elemind Neuromodulation headband is a wearable device that utilizes noninvasive, electroencephalography-based (EEG-based) technology to induce a sleep state more rapidly via personalized acoustic stimulation (see Fig. 1). Specifically, the headband uses a closed-loop system, meaning that the headband conveys stimulation based upon recorded neural activity in order to modulate real-time oscillating circuits at the macroscopic level [53]. Technologies that utilize closed-loop systems have been shown to be a superior approach to open-loop systems for disease treatment in prior work [54]. This device uses five dry, flexible EEG electrodes—including three recording electrodes that are positioned at the Fpz and Fp1/2 electrode sites in accordance with the 10–20 International System of electrode placement and two silicone rubber-based, linked reference electrodes located at the mastoids—to measure neural activity during sleep and provide an estimation of the phases of real-time neural oscillations [55, 56].

The headband generates a sound pulse by identifying alpha neural oscillations in real-time through endpoint-corrected Hilbert Transform algorithm, a signal processing advancement that is independent of oscillation sources and utilizes an infinite impulse response causal bandpass filter [53]. The headband furthermore utilizes a bone-conduction driver built into the center of the headband, which anatomically corresponds to the central forehead, to deliver auditory stimulation that is locked to phases of brainwave activity [55, 56]; this strategy has been found to impact continuous cortical oscillatory activity in prior studies [57, 58], including in older adults [57]. This method has, in turn, been shown to improve sleep for not only SWS oscillations [55, 57, 59] but also for oscillations across all sleep stages [56].

The Elemind Neuromodulation headband can be utilized in conjunction with machine learning approaches to optimize personalized treatments [53]. As such, the user-programmed device will use Bluetooth low energy or a direct USB-C connection to control the device and transfer data obtained by the headband to the Elemind application on a smartphone [55, 56], which will collect sleep metrics, including: (1) total sleep time, (2) sleep efficiency, (3) sleep architecture durations and percentage of total sleep time spent in each sleep stage (i.e., durations and percentage of total sleep time spent in the light (N1/N2), SWS, and REM stages of sleep); (4) sleep onset latency; and (5) restlessness (number of restless bout(s) per hour). The headband device will be supplied to participants at baseline and collected at the end of the study to analyze the sleep data. This intervention process will consist of two steps: (1) a period of data collection while participants initially wear the headband without stimulation for seven consecutive days and (2) subsequent data collection while participants continue wearing the Elemind Neuromodulation headband intervention with stimulation for at least 3 to 4 days per week throughout the 8-week duration. At the end of the analysis phase, the Elemind app will deliver a sleep report that includes a summary of each week’s aforementioned sleep data while the headband was in use. As each participant must have their own unique accounts to access the data associated with the utilization of the Elemind Neuromodulation device, there will be no data breach risk between participants who use the same Elemind device after each participant has completed the trial.

#### Lys

Lys is a coin-sized device which tracks lux and color levels through sensors aiming to replicate the eye’s photoreceptors. This device clips onto clothing or close-contact accessories (e.g., purse strap) and tracks light information throughout the day. The Lys devices measure the intensity, color, and duration of light exposure to gain insight into the relationship between light, sleep, circadian cycles, and energy levels. The Lys device communicates with the company’s proprietary app, named Insight, to display light exposure data to the user, as well as to provide the user with goals and insights related to light and health. The Lys device also communicates with a separate app, called Collect, which is used by the study team to download all data at the conclusion of the study. The Lys device has been validated in previous literature and has been used in other studies of this nature [60].

#### Quest Diagnostics blood draw

Participants will go to the nearest Quest Diagnostics location for blood sample collection. This de-identified data collected by Quest (i.e., biomarker data linked to a participant by a study identification number) will be consented to be shared by the participant to the study team. Cardiometabolic biomarkers will be collected and analyzed for all participants at the baseline and post-intervention visits, which will include a fasting lipid panel (comprised of total cholesterol, HDL, calculated LDL, and triglycerides) as well as markers of insulin resistance/glycemic dysfunction (C-peptide, insulin, HbA1c) and inflammation (hs-CRP). Moreover, holistic neurodegeneration and neuroaxonal stress will be assessed in all subjects via plasma NfL at baseline and at the post-intervention visit, which will be quantified using electrochemiluminescent immunoassay (ECLIA). In addition, all subjects will be assessed for AD-associated neuropathology at baseline, which will include plasma Aß1–42, Aß1–40, Aß1–42/Aß1–40 ratio, and p-tau217. Aß1–42 and Aß1–40 will be assayed via liquid chromatography-tandem mass spectrometry, the preferred and most accurate approach for amyloid quantification [61]. Furthermore, ECLIA will be utilized to quantify p-tau217. Additional details about how the AD-linked neuropathological biomarkers will be assayed are described elsewhere [62]. All Quest Diagnostics testing locations are appropriately licensed/certified under the Clinical Laboratory Improvement Amendments of 1988 (CLIA 88) and as required by certain State laboratory licensure programs. In addition, Quest Diagnostics’ Regional and Esoteric Reference Laboratories are accredited by the College of American Pathologists.

#### Cognitive assessments

The augmented reality platform delivers a Digital Neuro-Signature (DNS) based on > 700 sensor-derived digital biomarkers captured through brief (10–20 minutes), gamified cognitive tasks that simulate real-world activities [63]. The DNS has demonstrated high sensitivity (≈ 0.91) and specificity (≈ 0.82) in detecting MCI and early AD progression as well as a predictive accuracy of approximately 94% for conversion risk to AD within aging cohorts in prior work [64]. A longitudinal validation study (*N* = 525) showed strong correlations with traditional neuropsychological tests, such as the Mini-Mental State Examination (MMSE) and Montreal Cognitive Assessment (MoCA), and showed that DNS outperformed conventional tools in detecting early cognitive change [64]. The augmented reality-based Cognitive Assessment Platform provides reliable, ecologically valid cognitive phenotyping suitable for remote, high-frequency, digital health studies.

The DNS cognitive assessments, which are suitable for both iPhone iOS and Android devices, are augmented reality technologies that test a participant’s cognitive and functional aptitude via a self-learning (machine learning) algorithm. Cognitive scores will be assessed during baseline and follow-up on site or, for those in the sleep-only intervention group who are physically unable to come on site, at the participants’ homes using an application on a smart device. Participants will be asked to perform tasks using virtual reality representations on each subject’s smartphone’s camera. Using movement and response data plugged into machine learning systems, the service will provide a validated measure of MCI/AD risk, which will be shared with the study team and participants through a computer dashboard and through the app, respectively. The app will test all cognitive domains, but the three following cognitive function outcome variables, which are particularly susceptible to decline in MCI, will be considered the primary cognitive outcomes of interest in this trial: (1) spatial memory, (2) prospective memory, and (3) executive function. All other cognitive functions will be considered secondary outcomes of interest. All data will be automatically transmitted to the study team on an encrypted dashboard. The DNS cognitive assessments have been validated in previous literature [65].

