#### Cognitive pulse assessments

Participants will complete twice-weekly, brief cognitive pulse assessments using a digital cognitive tool, which will take approximately 10–20 minutes to complete. These will occur immediately after each in-lab exercise session in a designated testing space, enabling the study team to capture near-term changes in cognitive function related to exercise. Additionally, participants will complete the full-length digital cognitive assessments at week 0 (baseline) and week 8 in a quiet testing room. These assessments will simulate real-world cognitive tasks and will yield high-resolution, domain-specific cognitive profiles.

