#### Cognitive pulse assessments

Full-length, digital cognitive assessments (approximately 20 minutes) will be conducted at week 0 and week 8 in a quiet testing room at the University of Miami or, if unable to complete in person, via a secure video conference with a trained research assistant or postdoctoral fellow. Throughout the study duration, participants in this group will also complete brief, twice-weekly cognitive pulse assessments in each participant's  own home setting using the Digital Neuro-Signature Platform cognitive tool on two mornings per week after wearing the Elemind Neuromodulation headband the night before.

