#### Missing data and adherence

Participants missing ≥ 10% of required sleep intervention nights (defined as < 22 nights of wearing the sleep intervention over the 8-week intervention period) will be flagged for sensitivity analyses. If a participant misses > 2 consecutive weeks of data and/or fails to complete either of the full-length, digital cognitive assessments, such participants will be excluded from per-protocol analyses but retained in intention-to-treat models. Multiple imputations will not be applied due to the small sample size; instead, pattern mixture modeling or last observation carried forward (LOCF) methods will be used where applicable.

Adherence to the recommended neuromodulation utilization for the sleep intervention will be monitored via the Elemind application, which will log device usage and track sleep metrics. In addition, weekly phone or video check-ins (10–15 minutes) will be made to monitor engagement, support adherence, and troubleshoot technical issues. All reports of adherence will be documented upon the completion of each call/video check-in.

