#### Protocol structure and considerations

To reduce participant burden and improve standardization, in-lab exercise sessions and cognitive assessments will follow the same cadence and structure as in the exercise-only arm: twice-weekly, 60-minute, supervised sessions that will focus on aerobic and resistance training, home-based walking program, and brief digital cognitive assessments (the Digital Neuro-Signature Platform) immediately after each session. Participants will also wear the Elemind Neuromodulation headband for at least 3–4 nights per week across the 8-week period, with an initial 7-day, passive, onboarding screening phase of wearing the headband nightly without stimulation in combination with wearing the Fitbit device continuously to establish baseline sleep patterns, physical activity levels, and ensure that all eligibility criteria are satisfied. Finally, subjects will also wear the Lys device continuously throughout the 8-week trial period.

To manage cumulative burden, scheduling flexibility will be emphasized. Although participants will be offered a choice of days and times for in-lab sessions to fit each participant’s weekly routines, morning times will be strongly encouraged across all participants, as prior work has suggested that older adults generally show better cognitive and exercise performance in the mornings [42, 43]; this will further improve standardization. Staff will work closely with participants to accommodate visit times and ensure ample time for recovery between activities. Weekly adherence and well-being check-ins will be conducted and documented to monitor fatigue, motivation, and adverse effects.

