### Measures and instruments

To capture a comprehensive and multidimensional view of participants’ cognitive, emotional, behavioral, and physiological profiles, the study will employ both survey-based instruments and digital device-based measures. Instruments will be categorized into predictor and outcome variables and will span psychosocial, cognitive, behavioral, and biological domains.

Self-report surveys will be administered at baseline (week 0) and at the 8-week follow-up by a trained research assistant or postdoctoral scholar via in-person visits or, if unable to come in person in the sleep-only group, by a secure video conference. These will include the PASE [22] and CHAMPS [23] questionnaires to assess physical activity and weekly caloric expenditure, respectively, for those in the exercise-only or sleep + exercise interventions. Additionally, each participant will complete all validated Patient-Reported Outcomes Measurement Information System (PROMIS) short-form questionnaires that measure sleep disturbance, self-reported cognitive functioning, emotional support, depression, anxiety, life satisfaction, and social isolation [21] at the baseline and post-intervention visits, except for the General PROMIS Life Satisfaction 5a questionnaire, which will be completed at the baseline visit only. Additional measures will include a Demographic Questionnaire, a Chronic Health Questionnaire, and the Cross Ethnic-Racial Identity Scale [44] to capture relevant sociodemographic and psychosocial predictors (see Table 3). Objective data will be collected via digital devices, including the Elemind Neuromodulation headband (sleep metrics), Fitbit Charge 5 (physical activity and heart rate), Lys sensor (light exposure), and the Digital Neuro-Signatures neuropsychological assessment (cognitive function). Blood-based biomarkers will be obtained through Quest Diagnostics to assess brain and cardiometabolic health for all participants at the baseline and post-intervention visits as well as AD-associated neuropathology for all participants at the baseline visit. The 6MWT will be used to assess changes in fitness and aerobic capacity. Together, these tools will enable high-resolution modeling of the relationships between behavior, biology, and cognitive health across all three study arms.

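### Only the sleep-only arm has a remote route for the week-8 cognitive assessment, so cognitive primary outcomes may be missing more often in the two exercise arms

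*Protocol article*

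**What the plan says.** The place of the full-length cognitive assessment at weeks 0 and 8 is set arm by arm in the protocol article.

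- **Sleep-only.** The group 2 section on cognitive pulse assessments names a testing room or, "if unable to complete in person, via a secure video conference with a trained research assistant or postdoctoral fellow". The Cognitive assessments section repeats the home route but limits it to people "for those in the sleep-only intervention group who are physically unable to come on site".
- **Exercise-only.** The group 1 section states that "participants will complete the full-length digital cognitive assessments at week 0 (baseline) and week 8 in a quiet testing room". It gives no alternative.
- **Combined.** Under Protocol structure and considerations, "in-lab exercise sessions and cognitive assessments will follow the same cadence and structure as in the exercise-only arm". It gives no alternative either.
- **Surveys, all arms.** Measures and instruments provides for in-person visits or, "if unable to come in person in the sleep-only group, by a secure video conference".

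The Analysis plan counts the changes in cognitive scores among the primary outcomes. It tests them with a mixed model at baseline and week 8, the group × time term being the main test. Under Missing data and adherence, a participant who lacks a full-length assessment is "excluded from per-protocol analyses but retained in intention-to-treat models".

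**The concern.** The stated analytic goal is to find which arm improves most, so the arms should be measured under one rule. Here, of two participants equally unable to travel at week 8, one has a written way of being measured and the other does not, and the assigned arm alone decides which. Two sections name the sleep-only arm expressly, so this is a rule the article states and not a detail left to a fuller document.

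The restriction falls on the two arms with the heavier attendance load: two supervised sessions a week for 8 weeks, or 16 visits. If those who cannot attend have changed differently from those who can, the exercise and combined means describe the attenders more than the randomised group. That would distort the comparison of either arm with sleep-only. The trial is a pilot meant to supply effect sizes for a later trial, so a shift of this kind would be carried forward.

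**Working it through.** **1. What a missing week-8 score does in this model.** The primary model has two time points. A participant with baseline only stays in the likelihood and informs the baseline mean, but has no observed change. Intention-to-treat retention is therefore largely nominal for that participant's cognitive outcomes. Maximum likelihood, the method in the Analysis plan, relies on missing at random. If inability to attend is related to unobserved change, that assumption fails. If the last-observation-carried-forward option in the group 2 section were used instead, baseline would be carried forward as zero change, and more often in the exercise arms if they lose more week-8 scores.

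**2. Possible bias.** The article gives no dropout rate, and its sample-size section assumes no attrition. The rates below are my assumptions. Let q be the share of an arm missing at week 8, C the mean change in completers, and g the amount by which non-completers do worse, in SD of change.

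Full-arm mean = (1 − q)C + q(C − g) = C − qg, so the completers' mean overstates the arm's change by qg. I take the completers' mean as an approximation to the mixed-model estimate.

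With g = 0.5 and sleep-only q = 5%, the sleep-only shift is 0.05 × 0.5 = 0.025 SD.

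| Exercise-arm q | Shift in exercise arm | Between-arm bias |
|---|---|---|
| 10% | 0.050 SD | 0.025 SD |
| 20% | 0.100 SD | 0.075 SD |
| 30% | 0.150 SD | 0.125 SD |

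With g varied from 0.3 to 0.8 as well, the shift within one exercise arm runs from 0.03 SD (q = 10%) to 0.24 SD (q = 30%).

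**3. Precision of one pairwise contrast.** The SE of the difference in mean change, in SD units:

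- 20 versus 20: √(1/20 + 1/20) = 0.316.
- 16 versus 19 (20% and 5% missing): √(1/16 + 1/19) = 0.339.

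The central bias is 0.075 / 0.339 = 0.22 of that SE.

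**4. Power.** The plan states 60–65% for group × time. I could not reproduce this. A noncentral F with 2 and 57 degrees of freedom gives 93.2% with f² = 0.25 (noncentrality 0.25 × 60 = 15), or 37.4% if 0.25 is read as f (0.0625 × 60 = 3.75). That is a separate matter. Here I take the midpoint, 62.5%, at face value, with sleep-only differing from the other two arms, and remove week-8 data from the two exercise arms only:

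| Loss in exercise arms | n (sleep / exercise / combined) | Power |
|---|---|---|
| none | 20 / 20 / 20 | 62.5% |
| 10% | 20 / 18 / 18 | 60.6% |
| 20% | 20 / 16 / 16 | 58.4% |
| 30% | 20 / 14 / 14 | 55.8% |

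The cost is about 2 to 7 points, so comparability between arms is the main issue, not power.

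**5. Which comparisons are exposed.** Exercise-only and combined share the same site-based rule. The unequal rule therefore bears on each of them against sleep-only, not on the contrast between them.

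**The case against.** A reader might infer that anyone who stops exercise is lost from the primary endpoint. The article does not support that, for four reasons.

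- Nothing withdraws such a participant or bars the week-8 visit. The Analysis plan lists missing more than two weeks of intervention separately from missing follow-up cognitive assessments, and keeps both groups in intention-to-treat. Someone who stops in week 3 can still attend one visit in week 8.
- Only part of the primary outcome set is exposed. NfL and the cardiometabolic markers come from blood drawn at the nearest Quest location in every arm.
- The sleep-only route is for people unable to attend. A sleep-only participant who has merely lost interest is not clearly covered.
- Exercise-only pulse tests do stop with attendance ("These will occur immediately after each in-lab exercise session in a designated testing space"), but pulse scores are not in the primary model.

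All four stand, and they limit the point to participants who cannot come on site at week 8.

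It can also be said that the exercise section already requires a six-minute walk test after 8 weeks and that the combined-arm section cites standardisation, so testing on site is not arbitrary. That justifies the site as first choice. It does not explain why a fallback exists for one arm only, when the article describes the tool as suited to remote use on a smartphone.

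Finally, the bias figures are assumed and small beside the standard error. The exercise arms might lose more people under any rule, and a video option would recover only some of them. The article also allows pattern mixture modelling. This is fair: the calculation shows a possible size and does not predict one.

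**Conclusion.** The unequal rule is certain from the text; how much loss it will cause is not. Exercise-only and combined participants who cannot come on site at week 8 have no written route to the cognitive primary outcomes or the surveys, whereas comparable sleep-only participants do. A missing week-8 score leaves essentially no information on change. The resulting bias is unknown. It is about 0.075 SD if 20% versus 5% are missing and non-completers are 0.5 SD worse, and 0.025 to 0.125 SD if the exercise-arm rate is 10% to 30%. All of these attribute the whole difference in missingness to the assessment route, so they are illustrations on the high side of what the route alone would cause. The change is still worth making, because it is cheap and protects the main between-arm comparison.

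**What to change.** Write one rule for all three arms into the group 1, group 2 and group 3 sections on cognitive assessment, Measures and instruments, and Cognitive assessments:

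- Every randomised participant, including anyone who has stopped the intervention, is asked to complete the week-8 full cognitive assessment and surveys on site.
- Anyone who cannot attend uses the video or home route that already exists for the sleep-only arm. State the condition once, since the sections now word it differently.
- Record the mode (site or home) at each assessment and check whether the cognitive results are sensitive to it.

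The cost is protocol wording and one REDCap field, as the app and the video procedure are already in place. The downside is that a few exercise-arm assessments done at home add some mode-related measurement noise, which the recorded mode allows to be examined. No change to the pulse assessments is needed for the primary model.
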